### Data collection instruments

2.7

*First phase*: A sheet will be used to collect personal and sociodemographic data, complemented with clinical data according to the execution of medical examinations and interventions in the study participants.

Initially, it is intended to form the Group ii by searching people with VI from the Pedagogical of Support Center CAP-AC database, a public institution that exclusively provides socioeducational support services to low vision patients and the Centro de Saude Ocular (CSO), which is a private clinic of ophthalmologic care in Rio Branco City. Individuals for Group i those without VI who have good visual acuity will be invited from the CSO, seeking to match them as closely as possible with Group ii, regarding gender, age, occupation, etc.

After initial selection, volunteers will be submitted to routine clinical-ophthalmological examination, where aspects of general health will be investigated, as well as medication that may interfere with ANS, among others. Other aspects of eye health, such as visual acuity, corrective lenses, and history of ophthalmic surgery also will be evaluated.

Clinical and ophthalmological examinations that will indicate the study independent variables will be performed at the CSO, which has qualified human resources and medical equipment for anamnesis, visual acuity measurement, ocular pressure measurement, among others, with no costs for participants.

*Second phase*: In this phase, data of HRV will be collected. The protocol will be the same for both groups (Group i and Group ii). It will be divided in 3 moments of 15 minutes each: rest-intervention-recovery. After taking anthropometric measures, the participant of Group i will be given a brief rest in seated position, in a quiet environment, then the systolic, diastolic, and mean BP and HR will be measured to define a baseline condition (rest phase). Then, in the 2nd step or intervention phase, both eyes of the participant will be blindfolded with a sleeping mask that provides maximum occlusion (Fig. 5), remaining with vigilance and companionship.

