**Figure 6 F6:**
[figure not shown]
Educational toys.

At each stage of 5-minute intervention activities, the patient will be monitored for their systolic and diastolic HR and level of blood glucose.

In the 3rd phase called recovery with a duration of 15 minutes, the participants will sit relaxed and resting, continuing to monitor the collection of autonomic cardiac activity through the HRV.

Participants of Group ii, after verifying their anthropometric measures, will be submitted to the same protocol of Group i.

Measurements include systolic blood pressure, DBP, mean arterial pressure, HR, and blood glucose level.

The HR monitoring for further analysis of HRV will be obtained by an HR receptor RS800CX, Polar Electro, Finland. This device was validated to locate the heart beat for HRV analysis (Fig. 7). At the appropriate moment for collection during the estimated 45 minutes of evaluation, the strap will be placed on the chest of volunteers and the HR receptor (Fig. 8), which is an equipment previously validated for HR reception, beat and use these data for HRV analysis. The receiver temporarily stores the data that will then be processed on computers.

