**Figure 8 F8:**
[figure not shown]
Placement of the belt on the patient.

The recorded pulses will be directed to a computer through an infrared signal emitting interface for analysis of the HRV by Polar Precision Performance software. For data analysis, after storage in the software, they will be filtered at a moderate intensity for the elimination of ectopic beats and/or noises. The HRV analysis will be performed in time and frequency domain (linear analysis) and also by nonlinear analysis (Fig. 9).

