### Data analysis

2.8

Data will be analyzed using the Statistical Package for Social Science, version 22.0. Descriptive analysis will be performed for all variables. Data will be expressed as mean ± standard deviation or median (interquartile range), where appropriate. Sample distribution will be tested with the Shapiro–Wilk test. For comparison of initial and final values between groups, the unpaired Student *t* test for parametric distributions and the Mann–Whitney test for nonparametric distributions will be applied. Statistical significance will be considered at the level of *P* < .05 (or 5%).

As a risk measure, odds ratio will be calculated, adjusted, and not adjusted with their respective 95% confidence intervals. The odds ratio = 1 of lowest risk for the outcome of interest will be considered as the base category for each independent variable.

Statistically significant variables in the univariate analysis will compose the model for the multivariate analysis. In this multivariate analysis, multiple logistic regression will be used (Fig. 10).

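### The only adjusted analysis is logistic regression with odds ratios, but every measured response is continuous and no binary outcome is defined

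*Protocol article*

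**What the plan says.** Section 2.8 (Data analysis) of the protocol article has two parts.

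- **Unadjusted comparison.** "For comparison of initial and final values between groups", it uses the unpaired t test or the Mann-Whitney test, and it summarises data as mean and standard deviation or median and interquartile range. The responses are treated as continuous.
- **Risk analysis.** "As a risk measure, odds ratio will be calculated, adjusted, and not adjusted with their respective 95% confidence intervals". The reference rule follows: "The odds ratio = 1 of lowest risk for the outcome of interest will be considered as the base category for each independent variable". Covariates are chosen by screening: "Statistically significant variables in the univariate analysis will compose the model for the multivariate analysis". Then: "In this multivariate analysis, multiple logistic regression will be used".

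The responses are listed in section 2.7: "The HRV analysis will be performed in time and frequency domain (linear analysis) and also by nonlinear analysis", and "Measurements include systolic blood pressure, DBP, mean arterial pressure, HR, and blood glucose level". On the explanatory side, section 2.7 states: "Clinical and ophthalmological examinations that will indicate the study independent variables will be performed at the CSO". That sentence goes on to list visual acuity measurement among the examinations.

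**The concern.** Logistic regression needs a categorical dependent variable, here a binary one. The article refers to an outcome with a risk attached, but names no event and gives no threshold for any of the measured quantities. The model and effect measure therefore do not fit the responses the study collects.

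This matters because the groups are not formed by chance. One has normal vision and the other visual impairment, and matching is only as close as can be achieved. Adjustment is therefore needed to interpret a difference between them, and the logistic model is the only adjusted analysis offered. The abstract repeats the odds ratios as the analysis and mentions no adjusted comparison of means.

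**Working it through.** The article gives no power, effect size or standard deviation for its 50 + 50 participants, so there is no stated figure to reproduce. The check takes each way in which the logistic model could be run.

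**1. Types of variable.** HRV indices (time, frequency, nonlinear), systolic, diastolic and mean arterial pressure, heart rate and glucose (section 2.7) are all continuous. The only binary quantity defined in the text that could serve as a dependent variable for the study's comparison is group (sections 2.1 and 2.2).

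**2. Cutting a continuous response.** No cut-point is stated, so assume a median split of a normally distributed response. The asymptotic efficiency relative to a comparison of means is 2/π = 0.637.

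As a finite illustration, assume a standardised difference of 0.5, two-sided 5% and 80% power:
- Comparison of means: n = 2(1.96 + 0.84)²/0.5² ≈ 63 per group.
- After the split, the proportions above the cut are Φ(0.25) = 0.599 and 0.401. The pooled two-proportion formula gives 100 per group.
- The ratio is 63/100 = 0.63, in line with 2/π.

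The exact power loss at 50 per group depends on which test of proportions is used, so no single power figure should be relied on.

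**3. Using group as the dependent variable.** This asks what predicts visual impairment. The stated objective asks how cardiac autonomic activity behaves under acute and chronic loss of vision. There is also a technical obstacle:
- Section 2.2 puts acuity better than 20/30 in at least one eye in Group i, and best-eye acuity below 20/70 in Group ii, with a gap between.
- Section 2.7 lists acuity among the examinations that supply the independent variables.
- Entered in the model, best-eye acuity separates the groups completely, and the maximum-likelihood estimate does not exist.

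**4. The base-category rule.** The text does not say how the lowest-risk level is identified. Suppose it is read from the data. Assumptions: no true association, risk 50%, about 100 participants in k equal categories, log odds ratio with 0.5 added to each cell, and significance when |log OR / SE| > 1.96. The chance of at least one significant contrast, by simulation, is:

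| Levels k | Reference fixed in advance | Lowest observed risk as reference |
|---|---|---|
| 2 | 5.6% | 5.6% |
| 3 | about 7% | about 9% |
| 4 | about 9% | about 15% |
| 5 | about 12% | about 23% |

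With the data-chosen reference, no crude odds ratio falls below 1. The median over all contrasts under the null is about 1.3 (k = 2), 1.4 (k = 3), 1.6 (k = 4) and 1.8 (k = 5), against 1.00 with a fixed reference. For two levels only the direction flips, so the p value is the same.

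**The case against.** The strongest reply is that this is a condensed article. The full protocol, any SAP, Annex 4 and Figure 10 (cited at the logistic regression sentence) are not shown, and any of them could hold a cut-point. That stands. A reader might infer that no binary outcome exists, but the article supports only that none is defined. The reply does not remove the point, because a cut-point supplied elsewhere would still discard information from continuous responses in the only adjusted analysis.

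Four other stronger readings also go too far:

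- **That a fixed 50:50 group split makes odds ratios artefacts of sampling.** Sampling on group changes the intercept and leaves odds ratios intact. Matching distorts those for the matched factors (gender, age, occupation), not those for HRV, pressure or glucose, which could enter such a model uncut. The valid objections to group as outcome are the reversed question and the separation by acuity.
- **That the base-category rule pushes every odds ratio to 1 or above and invalidates every interval.** Adjusted odds ratios can fall below 1. Changing the reference level re-expresses the same model, so the fit and the overall test of a variable do not change, nor does a two-level p value.
- **That the reference is certainly chosen from the data.** The wording permits this without saying so. If the level were fixed on outside grounds, the inflation would not arise.
- **That the whole analysis fails.** The t test or Mann-Whitney comparison uses the continuous values and is untouched.

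**Conclusion.** The point holds, confined to the adjusted analysis. The stated model and effect measure do not match the stated responses, and neither way of making the model run is satisfactory. Cutting at the median costs roughly a third of the information (1 − 0.64 = 0.36, assuming normality and a median cut). Using group as outcome answers a different question and breaks down if acuity is included.

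The base-category rule is secondary and conditional. It raises false positives only for variables with three or more levels and only when the base is chosen from the data. The comparison must be like with like, any contrast against any contrast: at four levels that is about 9% to 15%, roughly a 1.6-fold rise. The 50% risk, equal categories and total of about 100 in that calculation are assumptions, apart from the total, which follows from 50 + 50.

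**What to change.** In section 2.8, and in the matching sentences of the abstract, replace the odds-ratio and logistic regression text with an adjusted analysis of the continuous responses. Use a linear mixed model with a participant effect and with group, phase (rest, intervention, recovery), group-by-phase and covariates named in advance. Report adjusted mean differences with 95% confidence intervals, or geometric mean ratios where HRV indices are log-transformed. Naming the covariates in advance replaces the screening by univariate significance.

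Fix the reference level of each categorical variable before data are seen. If a logistic analysis is kept as secondary, define its binary outcome and threshold beforehand and give the reason for the threshold.

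The unadjusted comparison can stay. The cost is analysis wording only: no change to recruitment, measurements or sample size. It should be settled before the data are analysed.

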**Figure 10 F10:**
[figure not shown]
General protocol flowchart.

## Discussion

3

Overall, in 2010, out of a total of 32.4 million blind and 191 million visually impaired, 0.8 million were blind and 3.7 million were visually impaired because of diabetic retinopathy (DR), with an alarming increase of 27% and 64%, respectively, in the 2 decades from 1990 to 2010. These numbers were lower in regions with younger populations (<2% in Southeast Asia and Oceania) than in high-income regions (North America, Western Europe, and Asia) with populations relatively aged (>4%).^[18]^

Dyslipidemia and hypertension may also influence DR, although in the context of individual patients, the associations between plasma lipids, lipoproteins, and DR are not strong enough to define the risk of retinopathy. Similarly, hypertension has been associated with increased risk of RD, and some data indicate that patients may benefit from the use of antihypertensive agents. However, recent studies have shown that more intensive BP monitoring does not confer additional benefits on the progression of retinopathy compared to standard follow-up. Taken together, the optimization of systemic risk factors is clearly important; however, even hyperglycemia (as measured by HbA1c) may represent only about 10% of risk of DR, and combined hypertension and dyslipidemia can lead to <10% risk in some cohorts. Such data strongly suggest that additional unidentified factors also play critical roles in the initiation and progression of DR.^[19]^

Universality is linked to the guarantee of the right to the same level of healthcare for all Brazilians, without any discrimination. It is very relevant researching about better ways of achieving positive results, new knowledge, and products that will improve the health of the population, either with a new diagnosis or new therapeutic treatments, or even with actions aimed at promoting the health of the population.^[20,21]^ The authors intend to propose a good quality protocol in its execution, having patient safety and demonstrating reliable information for healthcare area, contributing for better health care indicators of visually impaired people.

### Declaration, ethics approval, and consent to participate

3.1

This study will follow the guidelines that regulate human research in Resolution No. 466/12 of the National Health Council. We obtained approval from the Research Ethics Committee of Faculdade de Medicina do ABC, with CAAE: 73945017.0.0000.0082, and Opinion No. 2,275,101. All patients who agree to participate in the study will sign an informed consent form (FICF). The FICF is also available in audio and Braille versions. This study is registered in the Brazilian Registry of Clinical Trials under the number RBR-9sm9dp.

Temporary deprivation of vision pretends to simulate a fleeting “acute blindness” during 45 minutes to study the behavior of the ANS acting in the human heart, without significant risks to the participants and without waiting for natural events of sudden loss of bilateral vision.

Information and data collected will remain available to the participants in the archives of the institutions involved in the research, during and after the closure of this study.
